### Data collection and management

After the patient is determined to meet inclusion criteria and provides consent, the face-to-face survey is administered in English or Spanish in the ED and takes approximately 15 minutes, depending on responses and interruptions. Research assistants are trained to understand that data collection never interferes with medical care and the interview is stopped for any reason related to their care. The research assistant administers the baseline survey electronically on a table computer using Survey Monkey, an online survey tool. All protected health information is entered into a separate encrypted, password-protected database with only a unique linking identification number to match this information with that entered in Survey Monkey.

The survey includes questions regarding demographics, including gender, race/ethnicity, marital status, income, education, religious affiliation, type of residence, history of an advance directive or designation of a health care proxy, and health insurance; functional status is measured using the Eastern Oncology Cooperative Group score [8]; quality of life measured using the Functional Assessment of Cancer Therapy-General Measure [9]; and the Patient Health Questionnaire-9 [10] is used to screen for depression. Quality of life and depression are measured again at 6 and 12 weeks. The 6-week measurement was added one month into the protocol because a large proportion of our first participants died before the 12-week follow-up.

Six months after the ED visit, outcome data is collected via the electronic medical record and administrative data review using the *Mount Sinai Data Warehouse*. It provides content such as registration data, lab results, medications, radiology reports, procedures, and billing information. For the chart and administrative data review, a codebook was developed, inter-rater reliability was measured, and the research assistant performing chart abstraction was blinded to patient assignment.

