The goals of this study are: i) to test the feasibility of recruiting, enrolling, and randomizing patients with serious illness in the ED and ii) to evaluate the impact of ED-initiated palliative care on health care utilization, quality of life, and survival. To decrease bias in the measurement of baseline and outcome data, all study staff that perform patient follow-up, chart abstraction, or data analyses are blinded to patient assignment. We will measure the impact of the palliative care intervention on the following outcomes: i) timing and rate of palliative care consultation; ii) quality of life and depression at 12 weeks, measured using the *FACT-G* and *PHQ-9*; iii) health care utilization; and iv) length of survival.

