### Outcome measures

Outcomes were specified ahead of time, and include the rate and timing of palliative care consultation, quality of life and depression at 12 weeks, health care utilization, and survival. Independent variables are collected via a baseline interview with the patient or obtained from the electronic medical record, and are listed in Table 2. Dependent variables are listed in Table 3. The primary outcomes include rate and timing of palliative care consultation, quality of life and depression at 12 weeks, hospital length of stay, and survival. Secondary outcomes include costs during the index admission, ICU admission and ICU days, and ED revisits and re-hospitalization at 30 and 180 days. Objective outcomes were chosen that could be obtained from a chart or administrative data review to eliminate the possibility of recall bias or differential follow-up rates between the intervention and care-as-usual group.

**Table 2 T2:** Independent variables

**Variable**	**Measurement**	**Source**
Treatment group	Intervention, usual care	Research coordinator
Primary MD status	Full-time faculty/hospitalist, voluntary/private practice	Medical Record
Primary MD specialty	Heme/Onc, general medicine, other	Medical Record
Age	Years	Medical Record
Gender	Female, Male	Medical Record
Race/Ethnicity	Asian, Black, Hispanic Black, Hispanic White, Native American, White, Other	Patient Interview
Religion	Catholic, Protestant, Jewish, Muslim, Buddhist, Other, None	Patient Interview
Cancer diagnosis	Tumor type and stage	Medical Record
Performance status	ECOG Performance Status	Patient Interview
Medical comorbidities	Charlson co-morbidity index	Medical Record
Prior living situation	Home, nursing home, hospice	Patient Interview
Use of formal home care	Yes/no, Type of services, h/week	Patient Interview
Primary caregiver	Name and relationship/none	Patient Interview
Advance directives	Living will, health care proxy, power of attorney for health care/none	Patient Interview
Medical insurance	Medicare, Medicaid, Medicaid/Medicare managed care, Medicare managed care, traditional indemnity, self-pay, other	Administrative database, Medical Record

**Table 3 T3:** Dependent variables

**Variable**	**Measurement/Instrument**	**Source**

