**Primary Dependent Variables**		
Rate and timing of palliative care consultation	Yes/No; Days from enrollment to consultation	Medical Record
Quality of life	FACT-G at 12 weeks	Patient Interview
Depression	PHQ-9 at 12 weeks	Patient Interview
Hospital length of stay	Days during index admission	Medical Record
Survival	Days from enrollment	Medical Record

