### Analysis

We estimated our sample size based on one of our primary outcomes (time to palliative care) by utilizing data from the palliative care database on consultation in patients with advanced cancer. The baseline mean time to consultation for such patients seen by palliative care was 9 days (SD = 12). We estimated that our intervention would decrease this number by at least 50%, to 4.5 days (estimated SD = 6 days). Calculations employ two-tailed tests (α = 0.05, with β = 0.80). We plan to enroll and randomize at least 140 patients. We expect to have at least 80% power with α = 0.05 (two-sided) to detect clinically meaningful differences in these primary outcome variables with 70 subjects/group.

The primary analysis will be a traditional intention-to-treat that will compare intervention to control subjects on our predetermined primary and secondary outcomes. Two sample *t*-tests, Mann–Whitney, or *χ*^2^ will be used as appropriate depending on whether the outcome is continuous or discrete, and whether it is normally distributed. For the quality of life data, where there is a baseline score, ANCOVA will be used to compare outcomes between the two groups, and patients who die will be excluded from this analysis. A series of secondary analyses will be conducted if there is significant contamination between the intervention and control group. In the first of these sets of analyses, randomization assignment will serve as an instrumental variable and percentage of admissions receiving palliative care will be included as a covariate. We will also compare primary and secondary outcomes per protocol (i.e., patients will be grouped according to whether they received a consultation, rather than on their randomization scheme). We expect outliers in our outcome data and will not be excluding them from the analysis. Because of the small sample size, we will not account for permuted blocked randomization in the analyses.

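### Survival is a primary outcome with no stated horizon, yet it is read once per patient at six months; a single later vital-status check would probably recover information cheaply

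*Protocol article*

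**What the plan says.** In the protocol article, Outcome measures lists the primary outcomes, ending with "hospital length of stay, and survival". Background calls the survival outcome "length of survival". Table 3 measures it in "Days from enrollment", taken from the medical record, and gives no end date. The same table does attach 30- and 180-day windows to readmissions and repeat ED visits.

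Data collection and management describes one collection of chart and administrative outcomes: "Six months after the ED visit, outcome data is collected via the electronic medical record and administrative data review". The clock is each patient's own visit. No second vital-status check and no common cut-off date is described.

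Analysis names t-tests, Mann–Whitney and chi-square tests. The sample size comes from time to palliative care consultation, although the power sentence speaks of the primary outcome variables in the plural. No hazard ratio, median survival or accrual length appears anywhere.

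**The concern.** A six-month pull fits the 30- and 180-day counts. For survival it imposes, without saying so, a horizon that the outcome definition does not contain.

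Patients enter one at a time at a single center. When the last one reaches six months, the first has been at risk for six months plus the whole accrual period. Deaths in that extra time could appear in the record already being searched, but the described procedure does not look again.

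The precision of a survival comparison depends on the number of deaths. The Discussion says that the trial should supply effect estimates for designing a larger multicenter trial, so a less precise survival estimate has a real cost even in a pilot.

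**Working it through.** **The plan's own figure.** Inputs from Analysis: "The baseline mean time to consultation for such patients seen by palliative care was 9 days (SD = 12"), reduced "to 4.5 days (estimated SD = 6 days"); "Calculations employ two-tailed tests (α = 0.05, with β = 0.80"), where 0.80 is read as power; and "We plan to enroll and randomize at least 140 patients".

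- Pooled SD = √((12² + 6²)/2) = 9.487; difference = 4.5 days.
- n per group = 2 × 9.487² × (1.960 + 0.842)² / 4.5² = 69.8, so 70.
- Power at 70 per group = Φ(4.5 / (9.487 × √(2/70)) − 1.960) = 80.1%.

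The figure reproduces, but it concerns time to consultation and says nothing about survival.

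**Survival: inputs.** From the article: 70 per group, two-sided α = 0.05, six-month reading. Assumed, because the article gives none of them: exponential survival, proportional hazards, hazard ratio (HR) 0.7, 0.8 or 0.9, usual-care median 3, 4, 6 or 9 months, and uniform accrual over A = 12, 24 or 36 months.

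**Formulas.** λ₀ = ln 2 / median and λ₁ = HR × λ₀.

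- Expected deaths, six-month reading: 70 × [(1 − e^(−6λ₀)) + (1 − e^(−6λ₁))].
- Expected deaths, common date six months after the last enrollment: 70 × the sum over arms of 1 − [e^(−6λ) − e^(−(6+A)λ)]/(Aλ).
- Power = Φ(|ln HR| × √deaths / 2 − 1.96).
- Standard error (SE) of the log hazard ratio ≈ 2/√deaths.

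**Middle case (median 4 months, A = 24, HR 0.7).** λ₀ = 0.1733 and λ₁ = 0.1213 per month.

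- Six-month reading: 45.3 + 36.2 = 81.4 deaths. Power = Φ(0.3567 × 9.02/2 − 1.96) = 36%.
- Common date: 64.1 + 59.0 = 123.2 deaths. Power = Φ(0.3567 × 11.10/2 − 1.96) = 51%.
- The SE falls from 0.222 to 0.180, so the 95% limits narrow from ×/÷ 1.54 to ×/÷ 1.42.

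**Range at HR 0.7.**

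| Median, months | Deaths at 6 months | Deaths at common date (A = 12 / 24 / 36) | Power at 6 months | Power at common date | Gain, points |
|---|---|---|---|---|---|
| 3 | 96 | 122 / 130 / 133 | 42% | 51 / 53 / 54% | 8.9 / 11.4 / 12.4 |
| 4 | 81 | 112 / 123 / 128 | 36% | 47 / 51 / 52% | 10.7 / 14.5 / 16.1 |
| 6 | 62 | 93 / 109 / 118 | 29% | 41 / 46 / 49% | 11.8 / 17.3 / 20.1 |
| 9 | 45 | 74 / 91 / 103 | 22% | 34 / 40 / 44% | 11.1 / 17.6 / 21.6 |

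The smallest increase in deaths is 122.4/96.0 − 1 = 27.5% and the largest is 102.7/45.2 − 1 = 127%. The SE shrinks by 1 − √(96.0/122.4) = 11% to 1 − √(45.2/102.7) = 34%. A log-rank simulation with 3,000 runs per setting (medians 3, 6 and 9) gave gains of 9.9 to 21.3 points.

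**Other effect sizes, same medians and accrual.** The gain is 3.9 to 9.1 points at HR 0.8 and 0.9 to 2.3 points at HR 0.9.

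**If the effect does not last.** In simulation (HR 0.7 to six months, 3,000 runs per setting):

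- HR 0.85 afterwards, half the hazard reduction: power changes by less than 2 points in all 12 settings, for example 36% against 37% at a 4-month median with 24 months' accrual.
- HR 1.0 afterwards: power falls in all 12 settings, from about 43% to 32–36% at a 3-month median and from about 22% to 12–14% at a 9-month median.

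**Ceiling.** Even if all 140 patients die, 80% power needs HR = exp(−2 × 2.80/√140) = 0.62.

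**The case against.** - **The cut at six months is inferred.** A reader might conclude that the plan censors survival at 180 days or rules out later deaths. It says neither: Table 3 gives survival no horizon, and an article may leave the censoring rule to a fuller document. This stands. What can be said is that the only procedure described stops at six months.
- **The power figures are conditional.** A reader might take 9 to 22 points as an established loss. Hazard ratio, median and accrual are all assumed, and the Discussion says only that survival may increase. The upper end also sits poorly with the remark in Data collection and management that many of the first participants died before week 12 (about 2.76 months). A 9-month median implies 1 − 2^(−2.76/9) = 19% of usual-care patients dead by then, and a 3-month median 47%. At a 3-month median the gain is 9 to 12 points. This stands.
- **Longer follow-up can hurt.** The consultation is triggered at one ED visit, and usual-care patients may also receive one, so the contrast may fade. The simulation confirms that power can then fall. This stands and must be named with the fix.
- **Equal six-month follow-up suits the listed tests.** Mann–Whitney is then usable (simulated power about 22% to 38% at HR 0.7). With unequal follow-up the listed tests do not handle the censoring. This stands, so the fix has to change the method too.
- **Death capture may differ by arm.** Deaths come from the medical record, and intervention patients may be referred to the outpatient palliative care clinic. Longer follow-up gives record contact more time to diverge. This stands as a risk to check.
- **It is a pilot sized on another outcome.** True, and it lowers the stakes. But survival is listed as primary and the trial is meant to supply effect estimates, so precision still counts.

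**Conclusion.** The point holds as a cheap improvement. A fixed six-month window is a legitimate choice that costs efficiency; it is not a mistake. Followed as written, it leaves survival time unobserved beyond six months for all who are alive then, while the outcome definition sets no such limit.

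If hazards stay proportional, a common cut-off adds deaths and precision in every setting examined. The gain in power is worthwhile at a hazard ratio of 0.7, modest at 0.8 and negligible at 0.9, and its sign reverses if the effect disappears after six months. The article does not allow a choice among these cases.

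Nor should a reader infer that the change makes survival adequately powered. At a hazard ratio of 0.7 the best case is 54%, short of 80%.

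**What to change.** 1. State the survival cut-off in the protocol.
2. Keep the six-month pull for the utilization outcomes.
3. On one common date, six months after the last enrollment, query the same record and data warehouse for vital status and last-contact date of all randomized patients.
4. Compare survival by assigned arm with Kaplan–Meier curves and a log-rank test or Cox model, censoring patients not known to have died at last contact, in place of the listed tests for this outcome.
5. Report six-month survival beside it, so that a fading effect can be seen.
6. Compare last-contact dates between arms.

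Cost: one extra query for at most 150 patients, on the date when the last six-month review is due anyway. The trial is not lengthened and no patient contact is added. Downsides to name: dilution and lower power if the effect fades, and possible differences between arms in death capture over longer follow-up. The article reports that enrollment was still under way, so at that stage the change could be specified before the final data are seen.

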### Analysis

We estimated our sample size based on one of our primary outcomes (time to palliative care) by utilizing data from the palliative care database on consultation in patients with advanced cancer. The baseline mean time to consultation for such patients seen by palliative care was 9 days (SD = 12). We estimated that our intervention would decrease this number by at least 50%, to 4.5 days (estimated SD = 6 days). Calculations employ two-tailed tests (α = 0.05, with β = 0.80). We plan to enroll and randomize at least 140 patients. We expect to have at least 80% power with α = 0.05 (two-sided) to detect clinically meaningful differences in these primary outcome variables with 70 subjects/group.

The primary analysis will be a traditional intention-to-treat that will compare intervention to control subjects on our predetermined primary and secondary outcomes. Two sample *t*-tests, Mann–Whitney, or *χ*^2^ will be used as appropriate depending on whether the outcome is continuous or discrete, and whether it is normally distributed. For the quality of life data, where there is a baseline score, ANCOVA will be used to compare outcomes between the two groups, and patients who die will be excluded from this analysis. A series of secondary analyses will be conducted if there is significant contamination between the intervention and control group. In the first of these sets of analyses, randomization assignment will serve as an instrumental variable and percentage of admissions receiving palliative care will be included as a covariate. We will also compare primary and secondary outcomes per protocol (i.e., patients will be grouped according to whether they received a consultation, rather than on their randomization scheme). We expect outliers in our outcome data and will not be excluding them from the analysis. Because of the small sample size, we will not account for permuted blocked randomization in the analyses.

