## Methods

### Design

To evaluate the impact of ED-initiated palliative care consultation on quality of life, health care utilization, and survival on patients with advanced cancer, we are conducting a patient-level, single center, single blind pilot randomized controlled trial of 125 to 150 participants. The Institutional Review Board at the Icahn School of Medicine at Mount Sinai Hospital approved all study procedures (GCO 08–1234), and every participant provided informed consent.

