## Discussion

Here, we describe the design of a clinical trial to determine the impact of a palliative care intervention for advanced cancer patients in the ED on quality of life, depression, health care utilization, and survival. While this is a pilot trial to establish feasibility, it will provide an estimate of the effect of the intervention on our predetermined outcomes that can be used to inform the design of a larger multicenter trial.

Systematic reviews of palliative care have concluded that trials are sparse and findings limited due to methodological shortcomings inherent to this patient population [11]. Only a small proportion of the research in palliative care is based on clinical trials [12], as recruitment and retention of these patients for palliative care studies have proven challenging [13]. The ED setting adds other unique challenges not encountered in other settings. The environment is crowded and chaotic, and there is little privacy. Patients often have a high symptom burden and are in significant distress, all of which can preclude participation in research. The specificity of our environment, coupled with the lack of published clinical trials in palliative care, make the publication of our study protocol especially important to further research in this arena.

Visits to the ED for patients with advanced cancer are common, demonstrating the potential for altering the clinical course of these patients in this setting [14,15]. Despite this, there has been almost no needs-based research in palliative care and emergency medicine, and until recently little emphasis has been placed on education, research, or practice guidelines in end-of-life or palliative care in this important setting [16]. While some EDs are pilot testing palliative care programs, there has not been a structured and rigorous approach to the development and testing of such interventions to assure their success and test their impact on predetermined outcomes.

We hypothesize that ED-initiated palliative care consultation will increase the rate and decrease time to palliative care consultation, improve quality of physical and mental health, decrease health care utilization, and may even increase survival. We believe that it is not only feasible to enroll ED patients with serious illness in trials of palliative care, but that the ED presents a unique window in which to do so.

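### The trial is sized on days to consultation, which only consulted patients have, as if all 70 per group will have a value; and the planned minimum of 125 patients does not carry the stated 80% power

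*Protocol article*

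**What the plan says.** - **Sizing (Protocol article, Analysis).** The trial is sized on time to palliative care, one of several primary outcomes. The control figure comes from a database of consulted patients: "The baseline mean time to consultation for such patients seen by palliative care was 9 days (SD = 12"). The intervention figure is "We estimated that our intervention would decrease this number by at least 50%, to 4.5 days (estimated SD = 6 days"). The error rates are given as "Calculations employ two-tailed tests (α = 0.05, with β = 0.80"), and at least 80% power is claimed "to detect clinically meaningful differences in these primary outcome variables with 70 subjects/group".
- **Outcome (Table 3, Primary Dependent Variables).** Rate and timing are measured as "Yes/No; Days from enrollment to consultation".
- **Control access (Usual care).** Control patients may be consulted if the admitting team or the oncologist asks for it. No expected rate is stated.
- **Hypothesis (Discussion).** The authors expect that "ED-initiated palliative care consultation will increase the rate and decrease time to palliative care consultation".
- **Analysis.** The primary analysis is intention-to-treat, by t-test, Mann–Whitney or chi-square according to the type and distribution of the outcome. Nothing is said about patients who are never consulted.
- **Enrolment.** The Design section describes a "single blind pilot randomized controlled trial of 125 to 150 participants", and the Abstract gives the same range. The Analysis section says "We plan to enroll and randomize at least 140 patients".

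**The concern.** A patient who is never consulted has a No on the first half of the outcome and no number of days on the second. The planning mean and SD describe people who all had a consultation, yet they are applied to everyone randomised. The plan's own account of usual care, and its hypothesis of a higher rate under intervention, imply that some controls will lack a value.

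If the named tests are run on observed days, nearly the whole intervention arm is set against those controls whom a clinician chose to refer. Whether a control is referred is decided after randomisation and may depend on how ill the patient is, so randomisation no longer protects the comparison. If never being consulted is regarded as the longest wait, leaving those patients out also hides part of the effect that the trial looks for. The Discussion says the estimates will inform a larger multicentre trial, so the bias would carry into that design.

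The second problem needs no assumption about rates: two sections give different planned totals, and only one matches the power claim.

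**Working it through.** **Inputs from the Analysis section.** Control mean 9, SD 12; intervention mean 4.5, SD 6; difference 4.5 days; two-sided α = 0.05; power 80% (the article labels this β, a slip with no effect on the result); equal allocation.

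**1. The plan's figure reproduces.**
n per group = (1.96 + 0.8416)² × (12² + 6²) / 4.5² = 7.849 × 180 / 20.25 = 69.8, so 70.
Power at 70 per group = Φ(4.5/√(180/70) − 1.96) = Φ(2.806 − 1.96) = 80.1%. The Welch t-test gives 79.4%. There is no slack: all 70 in each group must have a consultation time.

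**2. Some controls without a time.** Keep 70 intervention patients, let n_c controls be consulted, and hold the planned means:
power = Φ(4.5/√(144/n_c + 36/70) − 1.96).

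| Controls consulted (assumed) | n_c | Two-means power | Mann–Whitney, lognormal times |
|---|---|---|---|
| 100% | 70 | 80.1% | about 98% |
| 90% | 63 | 76.7% | not needed |
| 60% | 42 | 62.0% | about 93% |
| 40% | 28 | 47.3% | about 85% |
| 30% | 21 | 38.1% | about 75% to 77% |

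The last column is by simulation, with lognormal times having the planned means and SDs (9/12 and 4.5/6). The lognormal shape is an assumption. Repeated simulations agree to within 1 to 2 points.

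**3. What the selection hides.** Under the same lognormal assumption, σ = √ln(1 + (12/9)²) = 1.011, and the median among consulted controls is 9/√(1 + 16/9) = 5.4 days. Suppose never-consulted controls count as waiting longer than anyone consulted. The median over all controls is then the 0.5/f quantile of the consulted times, where f is the share consulted:
- f = 0.90: the 55.6th percentile, 5.4 × exp(1.011 × 0.140) = 6.2 days.
- f = 0.60: the 83.3rd percentile, 5.4 × exp(1.011 × 0.967) = 14.4 days.
- f below 0.50: the median is never reached.

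A comparison among the consulted would work from 5.4 days in every case.

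**4. The two totals.** At 125 patients (62.5 per group), with a time for everyone: Φ(4.5/√(180/62.5) − 1.96) = Φ(2.652 − 1.96) = 75.5%, or about 74.5% by Welch t. At 150 patients: Φ(4.5/√(180/75) − 1.96) = 82.8%. The lower end of the range falls about 5 points short of the claim.

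**The case against.** Several points on the other side stand.

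- **The low power figures are t-test figures.** A non-negative time with mean 9 and SD 12 is skewed, and the plan chooses its test by normality, which points to Mann–Whitney. That test keeps more than 80% power in the table until somewhere between 40% and 30% of controls are consulted. With lognormal times and complete data it has about 96% at 62 and 63 patients per group.
- **The planned effect may be cautious.** The plan says at least a 50% reduction, and the Intervention arm section has patients seen on the same or the next day. With an assumed intervention mean of 1 day and SD of 1, the two-means power is about 99%, 94% and 86% at 42, 28 and 21 controls.
- **One all-patient comparison exists.** The Yes/No half of the outcome can be tested by chi-square on everyone randomised.
- **This is a pilot.** Leaving out never-consulted controls, seen as the longest waits, would understate the effect and not inflate it.

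A reader might also infer more than the documents support. They do not say that most, or even many, controls will go without a consultation, because no rate is given. Nor do they say that such patients will be dropped. The article is silent on how they are counted, and a fuller protocol or analysis plan may rank them last.

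What the objection leaves untouched is fixed in this article: a mean and SD from consulted patients set against a count of all randomised patients, and two planned totals that disagree. More power under Mann–Whitney does not cure selection on being consulted, and the chi-square test on the rate does not repair the timing outcome on which the trial was sized.

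**Conclusion.** The point holds in a limited form. The arithmetic behind 70 per group is right, but it describes a trial in which every patient is consulted, and the plan's own account of usual care says otherwise. Run on observed days, the named tests would not give the intention-to-treat comparison promised. That selection is the main harm.

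The effect on power depends on an unstated control rate and on the test. It ranges from a small shortfall (76.7% if 90% are consulted) to a large one (62.0% if 60% are) on the plan's two-means calculation, and there may be no shortfall at all with Mann–Whitney on skewed times. The conclusion that the trial is badly underpowered is therefore not supported.

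The conflict between 125 to 150 and at least 140 rests on the documents alone. On the stated inputs, 125 patients give about 75% power and not 80%. Again, this is a two-means figure and does not show that 125 patients would be too few for an outcome defined on everyone.

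**What to change.** 1. Define timing on all randomised patients. One option is the cumulative incidence of consultation from enrolment, with death as a competing event, compared by Gray's test. This suits a trial whose Data collection section reports that a large proportion of early participants died before 12 weeks. If consultation counts only during the index stay, discharge is a competing event too. A simpler option is Mann–Whitney with never-consulted patients ranked as the longest wait.
2. Report days to consultation among consulted patients as description only, without a test.
3. Reconcile the two totals. Either state that power is about 75% at 125 patients on the current calculation, or restate power for the all-patient outcome with the assumed consultation rates shown. As an illustration, 90% against 30% consulted (both assumed) gives power above 99% at 125 patients.

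The cost is wording and a restated power figure. Consultation and survival already come from the medical record, so no new data are needed, and enrolment need not rise. The trial was still enrolling at submission, so the rule could be set before analysis.

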#### Usual care

Patients assigned to the usual care arm complete the same baseline interviews and follow-up as intervention patients. If requested by the admitting team or oncologist of record, usual care patients may also receive a palliative care consultation.

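### The 80% power at 70 per group was calculated only for time to consultation; for FACT-G and PHQ-9 at 12 weeks the claim is unsupported and probably too high

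*Protocol article*

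**What the plan says.** All of this is in the protocol article.

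- **Basis of the sample size (Analysis).** "We estimated our sample size based on one of our primary outcomes (time to palliative care". The control input is taken from patients who were consulted: "The baseline mean time to consultation for such patients seen by palliative care was 9 days (SD = 12". The intervention is assumed to halve the mean to 4.5 days, with SD 6.
- **The power claim (Analysis).** The plan is to randomize at least 140 patients and to have "at least 80% power with α = 0.05 (two-sided) to detect clinically meaningful differences in these primary outcome variables with 70 subjects/group".
- **Primary outcomes (Outcome measures and Table 3).** These are rate and timing of consultation, FACT-G and PHQ-9 at 12 weeks, hospital length of stay, and survival. Only timing has a target difference and an SD.
- **Deaths.** The quality-of-life comparison is an ANCOVA using the baseline score, and "patients who die will be excluded from this analysis". Under Data collection and management, the reason given for adding a 6-week measurement is that "a large proportion of our first participants died before the 12-week follow-up".
- **Usual care.** If the admitting team or oncologist asks, "usual care patients may also receive a palliative care consultation".

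**The concern.** One outcome was calculated, but the claim is worded for several. For two of the others, the article's own text shows that the number in the claim cannot be the number analysed: FACT-G and PHQ-9 come from patient interviews at week 12, and the authors already knew of many earlier deaths. Consultations in usual care would pull the arms together on outcomes that a consultation is meant to change. The power sentence mentions neither effect.

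What is at stake is how a null result is read. A FACT-G or PHQ-9 comparison with no significant difference would be reported against a stated 80% power that was never derived for it. The Discussion says the results are to inform a larger multicenter trial, so readers should know which outcomes the pilot was sized for.

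**Working it through.** **1. The plan's own figure.** Inputs from the Analysis section: difference 9 − 4.5 = 4.5 days; SDs 12 and 6; two-sided α = 0.05; power 0.80 (printed as β = 0.80, which can only mean power).

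n per group = (1.960 + 0.842)² × (12² + 6²) / 4.5² = 7.849 × 180 / 20.25 = 69.8, so 70. Normal-approximation power at 70 is 80.1%; the pooled t-test gives 79.6%. The stated figure is reproduced. It is the bare minimum, with nothing added for death, loss or dilution.

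**2. What that figure assumes.** It needs a consultation time for all 70 patients in each group. If every intervention patient but only a fraction f of controls is consulted, SE = √(144/(70f) + 36/70) and power = Φ(4.5/SE − 1.960). The values of f are assumptions; the article gives none.

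| Controls consulted | n control | SE | Power |
|---|---|---|---|
| 100% | 70 | 1.604 | 80% |
| 80% | 56 | 1.757 | 73% |
| 60% | 42 | 1.986 | 62% |
| 50% | 35 | 2.151 | 55% |

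At 125 enrolled, the lower end of the range in the Design section (62.5 per group, all with a time), power is 75.5%.

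**3. FACT-G and PHQ-9 at 12 weeks.** No target difference, SD, death rate or baseline correlation is given. As a yardstick, take the standardized difference that a two-sample t-test detects with 80% power at 70 per group: d = 0.477. Then let a fraction m of each arm die before week 12 (assumed 20% to 50%), leaving n = 70(1 − m).

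- Unadjusted: two-sample t-test power at d and n.
- ANCOVA: the residual SD shrinks by √(1 − r²). At an assumed r = 0.5 the effective difference is 0.477/√0.75 = 0.551.
- Dilution: multiply d by 0.8 (an assumed 20% loss of effect through usual-care consultations).

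| Deaths | n per group | Unadjusted | ANCOVA, r = 0.5 | Unadjusted, 20% dilution | ANCOVA, r = 0.5, 20% dilution |
|---|---|---|---|---|---|
| 20% | 56 | 71% | 82% | 52% | 64% |
| 30% | 49 | 65% | 77% | 46% | 58% |
| 40% | 42 | 58% | 70% | 41% | 51% |
| 50% | 35 | 50% | 62% | 35% | 44% |

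ANCOVA makes up for the lost patients while m is at most about r², which is 25% at r = 0.5.

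**4. Detectable difference at 42 per group.** For 80% power: 0.62 SD unadjusted, or 0.62 × √0.75 = 0.54 SD with ANCOVA at r = 0.5.

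**The case against.** The strongest reply is that no shortfall has been demonstrated. That is right. The article does not define a clinically meaningful difference for FACT-G or PHQ-9, and the 0.48 SD yardstick is borrowed from the sample size. The remark on mortality concerns the first participants and gives no rate. A reader might infer that the design is shown to lack 80% power, or that power for quality of life is near a coin toss. The documents support neither: the figure is correct for the outcome it was derived from, and values near 50% arise only under particular assumed rates.

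The planned ANCOVA also matters. With an assumed correlation of 0.7, power for FACT-G stays above 80% up to 40% deaths (94%, 91%, 86% and 79% at 20%, 30%, 40% and 50%). However, the article specifies ANCOVA for the quality-of-life data and does not name depression there, and no correlation is given.

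The protocol does respond to both problems: it adds the 6-week measurement, and it plans instrumental-variable and per-protocol analyses if there is contamination. These are useful, but they do not restore power for the primary intention-to-treat comparison at 12 weeks.

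Finally, this is a pilot, and a later trial would draw mainly on its estimates and variability rather than on its power sentence. That limits the consequences. It does not excuse an affirmative power claim that the stated calculation does not cover.

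**Conclusion.** The concern holds in a limited form. The 70 per group is arithmetically right for time to consultation, provided that all patients have a consultation time. Extending the 80% to the other primary outcomes is unsupported, because no inputs are given for them. For FACT-G and PHQ-9 it also rests on an n that cannot be the analysed one, and it is probably too high.

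The size is conditional. Under 20% to 50% deaths, power for a 0.48 SD difference runs from 71% down to 50% unadjusted, and from 82% down to 62% with ANCOVA at r = 0.5. Adding 20% dilution to the ANCOVA case gives 64% down to 44%. Death rate, correlation and dilution are all assumptions.

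The two mechanisms should be kept apart. Consultations in usual care dilute FACT-G, PHQ-9, length of stay and survival. A reader might infer that they weaken the timing comparison in the same way, but its 9-day control mean already describes patients who were consulted. What erodes power there is controls who are never consulted.

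**What to change.** Rewrite the power statement in the Analysis section; no extra patients are needed.

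1. Restrict the 80% to time to consultation, and say that it assumes a consultation time for all 70 patients per group.
2. For FACT-G and PHQ-9, state the expected evaluable number per arm from the mortality observed so far, and the detectable difference at that number under the planned analysis. At 42 per group, for example, this is 0.62 SD unadjusted or about 0.54 SD with ANCOVA at a correlation of 0.5. Give the dilution assumption alongside.
3. Alternatively, label these and the remaining primary outcomes as exploratory estimates in this pilot.

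The cost is one revised paragraph and a less favourable stated power. The article reports that the trial was still enrolling at submission.
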